## Abstract

**Background:**

Geriatric patients with cognitive impairment (CI) show an increased risk for a negative rehabilitation outcome and reduced functional recovery following inpatient rehabilitation. Despite this obvious demand, evidence-based training programs at the transition from rehabilitation to the home environments are lacking. The aim of this study is to evaluate the efficacy of a feasible and cost-effective home-based training program to improve motor performance and to promote physical activity, specifically-tailored for post-ward geriatric patients with CI.

**Methods:**

A sample of 101 geriatric patients with mild to moderate stage CI following ward-based rehabilitation will be recruited for a blinded, randomized controlled trial with two arms. The intervention group will conduct a 12 week home-based training, consisting of (1) Exercises to improve strength/power, and postural control; (2) Individual walking trails to enhance physical activity; (3) Implementation of patient-specific motivational strategies to promote behavioral changes. The control group will conduct 12 weeks of unspecific flexibility exercise. Both groups will complete a baseline measurement before starting the program, at the end of the intervention, and after 24 weeks for follow-up. Sensor-based as well as questionnaire-based measures will be applied to comprehensively assess intervention effects. Primary outcomes document motor performance, assessed by the Short Physical Performance Battery, and level of physical activity (PA), as assessed by duration of active episodes (i.e., sum of standing and walking). Secondary outcomes include various medical, psycho-social, various PA and motor outcomes, including sensor-based assessment as well as cost effectiveness.

**Discussion:**

Our study is among the first to provide home-based training in geriatric patients with CI at the transition from a rehabilitation unit to the home environment. The program offers several unique approaches, e.g., a comprehensive and innovative assessment strategy and the integration of individually-tailored motivational strategies. We expect the program to be safe and feasible in geriatric patients with CI with the potential to enhance the sustainability of geriatric rehabilitation programs in patients with CI.

**Trial registration:**

International Standard Randomized Controlled Trial (#ISRCTN82378327). Registered: August 10, 2015.

## Background

The prevalence of cognitive impairment (CI) in patients admitted to geriatric rehabilitation units ranges from 30% to 80%, depending on sample characteristics and cut-off criteria [1, 2]. CI is accompanied with high demands for the health care systems, as decreased cognitive functioning is associated with increased care costs in this vulnerable population [3]. Compared to cognitively-intact patients, patient with CI show an increased number of risk factors affecting their health status, i.e., multi-morbidity [4], lower functional status [5], an increased risk of falling [6], and higher institutionalization and mortality rates [2]. Particularly, CI is often associated with specific motor-related symptoms, such as impaired functioning (i.e., deficits in balance and gait performance) [7–9], reduced participation in activities of daily living (ADL; i.e., shopping, dressing, or eating) [9] and reduced outdoor activities [10]. Further, a higher probability of neuropsychiatric symptoms is typical in patients with CI (i.e., apathy, anxiety, depression, irritability and agitation) [11–13], resulting in a loss of motivation to become physically active [14]. Patients with CI show an increased risk for negative rehabilitation outcome, leading to limited functional recovery during inpatient rehabilitation [15] and a lower functional status at hospital discharge [5]. Also, their access to medical services is limited, including post-ward rehabilitation (e.g., traveling too far to participate in rehabilitation programs is considered a typical barrier) [16]. These findings indicate the need for appropriate rehabilitation concepts for geriatric patients with CI at the transition from inpatient rehabilitation to their home environments and innovative, individually-tailored training concepts with low entry barriers are required. Effective post-ward rehabilitation programs may increase the ability to perform ADL, representing one of the most important predictor of societal costs of care of community-dwelling patients and improve functional performances and mobility (i.e., allowing proper preservation of autonomy).

Home-based training programs represent suitable exercise regimens that have been shown feasible and save in community-dwelling older adults with CI [17–21]. However, results of these home-based training programs are inconsistent. Some studies indicated improvements in motor performance [17, 18], while others only showed decelerated deterioration of physical function and mobility [22] or did not find any effects on performance [20, 21]. Further, studies showed methodological inconsistencies, e.g., not providing sufficient information on registered motor performance measures [20], not measuring key motor features (i.e., gait, balance, strength) as primary endpoints [19, 20], or using rather small sample sizes [18, 21].

Publications on home-based training programs in the vulnerable group of post-ward patients with CI are still scarce or inconclusive, despite overwhelming evidence based on supervised ward-based and post-ward programs are effective in improving motor function and physical activity (PA) in these specific population [23, 24]. Interventions at the transition from geriatric inpatient rehabilitation to the home environments have only been evaluated in heterogeneous patient populations [25–29]. Most programs included cognitively intact patients [25, 26] and only few studies integrated sub-groups of cognitively-impaired patients [27–29]. Some studies reported beneficial effects of home-based training on motor performance and mobility [25, 29], while others did not find training-related performance improvements [26, 27]. Furthermore, Moseley and colleagues indicated that patients with CI showed worse adherence rates compared to cognitive-intact persons during a home-based training program [27]. Hence, motivational strategies should be integrated into physical exercise programs to promote adherence and increase participation. The importance of motivational strategies is further emphasized by Heyn and colleagues [30], who explicitly state that previous interventions did not integrate appropriate motivational concepts to foster participation and enhance motivation in older adults with CI.

Surprisingly, behavioral aspects, such as PA have hardly been investigated in home-based training programs, although such behavioral changes are crucial for the sustainability of rehabilitation programs. Primary aim of most programs was to improve motor performance and only a few studies documented PA using questionnaires [17, 18, 21]. None found training-related improvements and none objectively registered PA using sensor-based assessment strategies. The latter is astonishing since, due to recall and response bias, questionnaire-based assessments are less valid and reliable in cognitively-impaired older adults [31]. Thus, assessment strategies including objective sensor-based as well as subjective questionnaire-based measurements are advised to comprehensively register changes in activity behavior following training interventions.

The current study protocol addresses the situation of multi-morbid and frail geriatric patients with mild to moderate CI following inpatient rehabilitation. Primary aim of the study is the development and evaluation of a safe and feasible home-based exercise program to improve motor performance and to promote PA (i.e., initiate sustained behavioral changes) in the vulnerable group of multi-morbid, geriatric patients with CI, suitable to be implemented in existing health care plans.

## Methods/Design

### Study design

The presented study is a blinded randomized-controlled trial (RCT) with two arms (i.e., an intervention group [INTV] and a control group [CTRL]; Fig. 1) and will be implemented according to CONSORT guidelines [32]. Ethical approval according to the ethical standards of the Helsinki declaration was obtained from the internal review board at the Medical Faculty of the University of Heidelberg, Germany (reference#: S-252/2015). The study protocol has been registered with the “International Standard Randomized Controlled Trial Number” (ISRCTN) trial register (http://www.isrctn.com/ISRCTN82378327).

**Fig. 1 Fig1:**
[figure not shown]
Schematic illustration of the study design

### Sample characteristics

Inclusion criteria are (1) patients admitted to ward-based rehabilitation in a geriatric hospital in Heidelberg, Germany; (2) age ≥ 65 years; (3) mild to moderate CI (Mini-Mental-State-Examination [MMSE]: 17–26); (4) ability to walk 4 m without support; (5) residency within 30 km of the study center; (6) discharge from rehabilitation unit to home environment; (7) no terminal disease/no delirium; (8) German-speaking; and (9) written informed consent from participant or care giver. All patients admitted to the geriatric inpatient rehabilitation at the AGAPLESION Bethanien Hospital are consecutively screened for inclusion.

### Measures

After inclusion of the participants, primary and secondary outcome parameters are registered at baseline (T1), following the training intervention (T2), and 12 weeks after the training is completed (T3). At baseline, additional descriptive parameters (i.e., age, gender, height, weight, Barthel Index) are registered. Blinded assessors will conduct the measurements at the patients’ home.

### Motor performance

Key motor performances will be assessed using the Short-Physical-Performance-Battery (SPPB) including sub-tests of static balance, walking performance and sit-to-stand performance [33]. Outcome parameters are the total SPPB score (i.e. 0–12 scores) calculated as the summation of each sub-test score and the scores in each of the sub-tests (i.e. 0–4 scores) [33]. The “Timed Up and Go-test” (TuG) is performed to assess basic functional mobility [34]. Outcome parameter is the time in seconds needed to perform the task.

Additionally, objective performance measures are registered for SPPB using advanced body-fixed motion sensors (DynaPort MT, McRoberts B.V., The Hague, Netherlands). The sensor is attached to subject’s lower back at the height of the second lumbar vertebra. The measurement system (106.6 × 58 × 11.5 mm, 55 g) contains three pre-calibrated seismic accelerometers (sensor range: ± 2 g, resolution: 1 mg) and three gyroscopes (range: ± 100 deg./s, resolution: 0.0069 deg./s). Data is recorded at a sampling rate of 100 Hz. Outcome parameters are defined as body sway in terms of Center of Pressure (CoP) displacements in mm and CoP velocity in mm/s to evaluate static balance performance. During the 5-times-chair-rise test, sit-to-stand and stand-to-sit durations in seconds and maximum angular velocities in deg./s are calculated.

### Physical activity

PA will be registered using a small-scaled (51 × 30 × 16 mm, 24 g) activity monitor (PAMSys, BioSensics, Cambridge, MA, USA), attached on subjects’ chest using adhesive bands. The activity monitor includes a tri-axial accelerometer sensor registering accelerations in three perpendicular directions (accelerations in the frontal, vertical, and lateral directions) at a sampling frequency of 40 Hz. Additionally, a second activity monitor (uSense) will be used for validation purpose. The uSense sensor is a non-commercial prototype, developed by the EU-funded “FARSEEING” project allowing detailed quantitative as well as qualitative data analysis. The sensor (42 × 10 × 68 mm, 36 g) includes a 9-axis inertial platform (accelerometer, gyroscope, magnetometer) registering acceleration and orientation in X, Y and Z direction at a sampling frequency of 100 Hz and is attached to subjects’ lower back using adhesive bands.

Raw data from both activity monitors is transferred to a stationary computer for offline analysis using established algorithms [35]. Outcome parameters are number and duration (registered in minutes) of postural episodes (lying, sitting, standing, and walking), cadence defined as steps per minute, number of steps (i.e., total number of steps, number of steps per gait episode) and sit-to-stand/stand-to-sit transitions (number of sit-to-stand/stand-to-sit transitions). The uSense sensor additionally registers qualitative gait parameters (e.g., mean step duration [s], step regularity [%], turning velocity [deg/s]) during each walking episode. Participants are asked to wear the monitor continuously for 48 h.

### Life-space

The University of Alabama at Birmingham Study of Aging Life-Space Assessment has been used to document the mobility of community-dwelling older people [36]. Life-space zones range from a person’s bedroom (level 0) to beyond the person’s home town (level 5). For each life-space zone, subjects report how often they travel to that area per week and whether they need assistance. Higher scores indicate high life-space mobility from 0 (“totally bed-bound”) to 120 points (“traveled out of town every day without assistance”) [36]. We developed a modified version of the University of Alabama at Birmingham Study of Aging Life-Space Assessment to assess participants’ life-space (LSA). The LSA is adjusted to specific limitations of patients with CI to eliminate recall bias and has been successfully validated in geriatric patients with CI (paper submitted).

Additionally, participants’ outdoor life-space will be objectively measured using a Global Position System (GPS) tracker. Participants are asked to wear the mobile GPS tracker (QStarz BT1000X, Qstarz International Co., Ltd., Taipei, Taiwan) for 48 consecutive hours. Using a sampling rate of 0.2 Hz, the GPS tracker records participants’ outdoor location (i.e., longitude and latitude coordinates) with an accuracy of ±5 m. Outcome measures for a patient’s life-space are total LSA score, the maximum distance in meters from the participant home and the mean distance of outdoor walking episodes in meters assessed by GPS using location data [37].

### Psycho-social parameters

#### Health-related quality of life – EuroQol - 5 Dimensions (EQ-5D):

The EQ-5D, including five health-related domains (mobility, self-care, pain/discomfort, usual activities and anxiety/depression) will be used to measure health-related quality of life [38]. Outcome parameters are the EQ-5D total score (5–15 points) and participants’ self-rated perceived health status (0–100 points).

#### Geriatric Depression Scale – Short Form (GDS-SF):

The 15-item GDS-SF will be used to register depressive symptoms [39] by assessing their presence/absence in frail older people (e.g. “Are you basically satisfied with your life?” or “Do you feel happy most of the time?”) [40]. A total score of 0–15 points can be achieved with higher scores representing a higher probability of depression (i.e., total score > 5 points indicates mild depressive symptoms, a total score ≥ 10 points indicates moderate to severe depression) [39].

#### Apathy Evaluation Scale-Clinical version (AES-C):

The 18 item AES-C will be used to evaluate participants’ for apathy [41]. The AES-C defines apathy as a psychological dimension based on deficits in behavioral, cognitive, and emotional circumstances of goal-directed behavior. Using the AES-C, the evaluation of apathy is based on clinical observations and subjects’ self-reports during a semi-structured interview. A total score of 0 to 54 points can be achieved with higher scores representing a higher probability of apathy.

### Fall-related parameters

#### Fall history:

Falls are defined as an unexpected event where a person comes to rest on the ground, floor or lower level [42]. We will assess the number of falls prospectively during the intervention period using diaries administered by the participants and weekly phone calls conducted by the trainer [43]. Fall history of patients is registered retrospectively at T1, T2 and T3 by asking the participants how often he/she fell during the preceding 4 weeks and 12 months. At T3, participants are additionally asked how often he/she fell during the preceding 12 weeks between T2 and T3.

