### Secondary outcomes

*motor performance:* SPPB sub-test scores (0–4 points each), TuG total time, sensor-based parameters during SPPB sub-tests (e.g. CoP displacements, CoP velocity, sit-to-stand and stand-to-sit duration, maximum angular velocities), and qualitative gait parameters (e.g., mean step duration, step regularity, turning velocity)
*physical inactivity:* duration of inactive episodes (i.e., sum of lying and sitting), quantitative gait parameters (i.e., cadence as steps per minute, total number of steps, and number of steps per gait episode)
*life-space:* LSA total score (0–90 points), maximum distance from home and mean walking distances (GPS-based measurements)
*quality of life:* EQ-5D total score (5–15 points), VAS score (0–100 points)
*psychosocial status:* GDS-SF total score (0–15 points), AES-C total score (0–54 points), FES-I total score (7–28 points), FFABQ score (0–56 points)
*falls*: fall history, number of falls during the intervention period
*short-term working memory:* WAIS-IV test performance (0–9 points)
*cost evaluation:* ICER for operational as well as health care costs

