### Intervention

Participants in INTV take part in a standardized 12-week home-based training program. The program is specifically-tailored for geriatric patients with CI after post-ward rehabilitation to improve motor performance and enhance PA. The training intervention was derived from an exercise program developed by our research group, which was feasible and effective to increase strength and functional performances in patients with CI [24]. Based on results of a successfully conducted home-based exercise pilot RCT, our program includes six exercises to improve static and dynamic postural control (i.e., standing and walking) and strength (i.e., tiptoe stance, stair climbing, sit-to-stand transfers). Exercises are explained and regularly reviewed by a professional trainer and illustrated at the patient’s home using a large poster (84.1 × 59.4 cm; Fig. 2). A brief description of key elements for each exercise is provided using a printed manual. Training progress and adherence is supervised by weekly phone calls and regular home visits of the trainer (5 visits in 12 weeks).

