### Statistical analysis and sample size

An intention to treat analysis will be conducted. We performed an a priori power analysis to determine the sample size necessary to obtain significant effects in PA. Power analysis for PA is difficult to calculate since studies using identical sensor-based physical activity assessments in cognitively-impaired geriatric patients have not been available. Thus, the effect size is based on a study conducting a functional strength training program in 137 institutionalized patients [54]. PA, as assessed by the MTI Actigraph, showed an average increase of PA by 43% in the strength training group compared to a control group (effect size: eta^2^ = 0.18). A priori power analysis was performed using GPower 3.1 software [55]. A repeated measure analysis of co-variance (ANCOVA) design including two groups and two repeated measurements yielded a total sample size of *N* = 101 (α = 0.05; critical F = 2.69). Estimating a drop out of 15%, we will recruit a total of 116 participants. For motor performance, as assessed by the SPPB total score, a pilot study conducted by our research group showed that performance improvements can be achieved using relatively small sample sizes (*N* = 34; large effect size: eta^2^ = 0.22 [56]). Repeated measures ANCOVA will be used to determine effects of the home-based training program on primary and secondary outcomes for effects of intervention (T1-T2) and sustainability of effects (T1-T3). Effect sizes are determined by calculating eta^2^ [57]. All data will be analyzed using SPSS 23.0 (SPSS Inc., Chicago, Ill., USA).

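### The 12-month fall recall at T2 and T3 is unsuitable as an outcome, and the stated repeated measures ANCOVA cannot be formed for the better fall counts

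*Protocol article*

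**What the plan says.** Under Fall history, the protocol article collects falls in four ways:

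- A prospective count: "We will assess the number of falls prospectively during the intervention period using diaries administered by the participants", supported by weekly trainer calls.
- A 4-week recall at T1, T2 and T3.
- A 12-month recall at the same three visits. Both recalls come from "asking the participants how often he/she fell during the preceding 4 weeks and 12 months".
- One further recall: "At T3, participants are additionally asked how often he/she fell during the preceding 12 weeks between T2 and T3".

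Secondary outcomes has two fall entries, "fall history, number of falls during the intervention period". It does not say which recall window defines the first.

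Statistical analysis and sample size states that "Repeated measures ANCOVA will be used to determine effects of the home-based training program on primary and secondary outcomes", for T1-T2 (effect) and T1-T3 (sustainability). It makes no exception for counts.

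On timing, Intervention says "Participants in INTV take part in a standardized 12-week home-based training program", and Measures places the later visits "following the training intervention (T2), and 12 weeks after the training is completed (T3". T2 is therefore at about week 12 and T3 at about week 24.

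**The concern.** A 12-month recall taken 12 or 24 weeks after baseline mostly asks about falls that the program could not have influenced. Much of the same period was already counted at T1, so a T1-T2 or T1-T3 change in this item compares two overlapping periods.

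The stated model adds a second difficulty, because it needs the same measure at T1 and at the later visit. Of the four fall measures, only the 4-week and 12-month recalls meet that condition. The prospective count, which is the best fall measure and a named outcome, does not. Read literally, the analysis sentence steers the falls comparison towards recall items, in a population for which the Background section says that "due to recall and response bias, questionnaire-based assessments are less valid and reliable in cognitively-impaired older adults".

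Falls are the only harm-type entry in the outcome list, and the program encourages frail patients to exercise and walk outdoors independently. A clear between-group estimate of the fall rate is therefore worth having, even as a secondary result.

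**Working it through.** The protocol gives no figure for falls, so there is none to reproduce.

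**Inputs.** T2 is at week 12 and T3 at week 24 (Measures, Intervention). The recall window is 52 weeks (Fall history). The date of randomization relative to T1 is not stated, so T1 serves as the start of the post-baseline period.

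**Step 1: share of the 12-month window before T1.** With w weeks elapsed since T1, the share is (52 − w)/52.

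- T2: (52 − 12)/52 = 40/52 = 76.9%
- T3: (52 − 24)/52 = 28/52 = 53.8%

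The same 40 and 28 weeks also fall inside the 12-month window asked at T1.

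**Step 2: effect on a ratio of 12-month totals.** With a constant underlying rate, the apparent ratio is [(52 − w) + w × RR]/52.

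| True RR | At T2 | At T3 |
|---|---|---|
| 0.50 | 0.88 | 0.77 |
| 0.70 | (40 + 12 × 0.7)/52 = 0.93 | (28 + 24 × 0.7)/52 = 0.86 |
| 0.80 | 0.95 | 0.91 |
| 1.50 | (40 + 12 × 1.5)/52 = 1.12 | (28 + 24 × 1.5)/52 = 1.23 |

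**Step 3: effect on a mean difference, which is what ANCOVA estimates.** With weekly rate λ and comparable arms at T1, the expected 12-month count at T2 is 52λ in control and 40λ + 12λ × RR in intervention. The difference is 12λ(RR − 1), exactly that of the 12-week prospective count. The pre-baseline weeks cancel in expectation. They leave the mean difference unchanged but add variance.

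**Step 4: cost in power.** The protocol gives no fall rate or dispersion. Assumed: 1.5 or 3 falls per person-year, gamma frailty variance 1, true RR 0.6 over all post-baseline time, 50 per arm, 1,500 replicates. Every analysis adjusts for the T1 12-month count (on the log scale in the quasi-Poisson model).

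| Measure and model | 1.5 falls/year | 3 falls/year |
|---|---|---|
| 12-month recall at T2, ANCOVA | 0.12 | 0.23 |
| Prospective 12-week count, ANCOVA | 0.21 | 0.39 |
| Prospective 12-week count, quasi-Poisson | 0.20 | 0.39 |
| 12-month recall at T3, ANCOVA | 0.24 | 0.43 |
| 24-week post-baseline count, quasi-Poisson | 0.36 | 0.61 |

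With RR = 1, ANCOVA rejected in 4.5% to 5.7% of replicates. At T2, where window and model can be separated, the loss comes from the window. The T3 rows change both at once.

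**Step 5: can the stated model be formed?**

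| Measure | T1 value of the same kind? | Wholly after T1 at T2/T3? |
|---|---|---|
| 12-month recall | yes | no |
| 4-week recall | yes | yes |
| Prospective T1-T2 count | no | yes |
| 12-week T2-T3 recall | no | yes |

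The last two rows cannot enter a T1-T2 or T1-T3 repeated measure. The ANCOVA rows for the prospective count in Step 4 use a different measure (the T1 12-month count) as covariate, which is a sensible analysis but not the repeated-measures form in the text. The 4-week recall fits the model but covers only 4/12, one third, of the intervention period.

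**The case against.** A reader might infer that the falls comparison as a whole is diluted and that a real rise or fall in falls would be hidden. The protocol does not support that. The prospective count is a separately named outcome, and it, the 4-week recall and the T2-T3 recall all lie wholly after baseline. Nor does the plan say that fall history means the 12-month item. It leaves the window open.

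A reader might also take 0.93 and 0.86 as the bias of the planned analysis. They are not, because they describe ratios of 12-month totals and the planned ANCOVA estimates a mean difference (Step 3). They also assume a constant fall rate before and after T1, which is uncertain in patients who have just left inpatient rehabilitation.

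Third, one might call ANCOVA invalid for these counts. In the simulation it kept its type I error near 5% and matched quasi-Poisson in power on the same count. The analysis sentence is also generic: taken literally it would cover the cost-effectiveness ratio as well, and outcome-specific models are commonly left to an analysis plan.

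All three points stand as limits. They do not rescue the 12-month item at T2 and T3, and they do not supply the missing T1 value for the prospective count. The article does more than stay silent on the model: it names one, and that model does not fit. It also yields no rate ratio and makes no allowance for observed time, although the protocol itself expects 15% drop-out.

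**Conclusion.** The point holds in a limited form. The 12-month recall at T2 and T3 is a poor outcome: about 77% and 54% of its window precedes T1 and overlaps the T1 window. Under the assumed rates and a true RR of 0.6, power at T2 falls from about 0.21 to 0.12, or from 0.39 to 0.23, compared with the prospective count under the same model. The stated repeated measures ANCOVA cannot be formed for the prospective count or the T2-T3 recall.

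The documents do not support a claim that falls as a whole are diluted or hidden, or that the error rate is inflated. The window shares rest only on the visit schedule, with T1 as the start of the post-baseline period. The power figures rest on assumed fall rates, dispersion and effect. Falls are secondary and the trial is not sized on them, so the practical weight is moderate. The change is worth making because it is nearly free.

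**What to change.** - Ask the 12-month recall only at T1, and use it as a descriptor and covariate.
- Define two between-group fall outcomes: the prospective diary and call count from T1 to T2, and the 12-week count from T2 to T3 already asked at T3. State that the second still rests on recall.
- Analyse each by negative binomial or quasi-Poisson regression with log observed time as offset and T1 fall history as covariate. Report rate ratios with 95% confidence intervals.
- Keep the 4-week recall as supportive, and name the window wherever fall history appears as an outcome.
- Exempt these counts from the repeated measures ANCOVA sentence.

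The cost is a change of wording and slightly more analysis work. No new data are needed, and the 12-month question can be dropped at two visits. Precision will stay low: even the prospective 12-week count had power of only about 0.2 to 0.4 in the scenarios above, so the result should be read as an estimate with its interval and not as a test.
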